**Methods::**

This is a prospective randomized controlled trial to study the efficacy and safety of Shenfu injection combined with furosemide in the treatment of coronary heart disease and chronic heart failure. This study will be approved by the clinical research ethics committee of our hospital. The patients will be randomly divided into two groups according to 1:1:(a) Shenfu injection combined with furosemide group and (b) simple furosemide group. Standard treatment for 7 days followed up for 30 days at the same time, pay attention to its efficacy and safety indicators. The total effective rate of cardiac function improvement, left ventricular ejection fraction (LVEF), N-terminal pro-brain natriuretic peptide (NT-pro BNP), 6-minute walk test (6-MWTD), and adverse reactions will be observed. Data will be analyzed using the statistical software package SPSS version 25.0 (Chicago, IL).

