### Study design

2.5

In this study, patients who meet the criteria will be screened through pre-hospital recruitments and in-hospital inpatients. The patients and their families will approve the study program and sign the informed consent form. The observation group will receive SFI (SFI 50 mg / kg CS100 ml, ivgtt, qd) combined with furosemide injection (Furosemide 20 mg / kg GS 250 ml, ivgtt, qd), while the control group will only receive furosemide injection (Furosemide 20 mg / kg GS 250 ml, ivgtt, qd). Patients in both groups will receive the same routine care and drug treatment, such as angiotensin converting enzymeinhibitiors (ACEIs) or angiotensin II receptor blockers (ARBs). If necessary, the attending physician can adjust the plan according to the patient's condition, and all interventions will be recorded in detail for final result analysis. We will set up a special drug manager, and the nurse will be responsible for preparing the medicine, preparing the solution, and using the disposable optical infusion device to infuse the corresponding numbered patients. Therefore, the study is not blind to nurses, but to researchers, patients, and statisticians. All patients will receive intravenous injections once a week. The health status of each patient will be evaluated before and after treatment, including efficacy and safety indicators, and all patients will be followed up for 30 d by telephone or outpatient clinic. Follow-up will include cardiovascular events and rehospitalization.

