### Data collection and management

2.7

Data will be collected before treatment, 72 hours after treatment, and at the end of treatment according to evaluation criteria. After 30 days of treatment, outpatient or telephone follow-up will be conducted for each patient. Detailed follow-up information can not be collected to record the reasons for loss of follow-up information. All data will be collected by one or two assistants. Personal information about potential and registered participants will be collected, shared, and kept in a separate storeroom to protect confidentiality before, during, and after the trial. Access to the database will be limited to the researchers of this research group.

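### Section 2.5 gives two incompatible infusion frequencies, daily and weekly: 7 infusions or 1 on the abstract's 7-day course

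*Protocol article*

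**What the plan says.** Section 2.5 (Study design) defines the two arms. The observation group receives Shenfu, written as "SFI 50 mg / kg CS100 ml, ivgtt, qd", together with furosemide, written as "Furosemide 20 mg / kg GS 250 ml, ivgtt, qd". The control group receives furosemide alone, with the same order repeated. Every drug order is therefore once daily.

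Further on in section 2.5, after the paragraph has described who prepares and gives the infusions, it says: "All patients will receive intravenous injections once a week". No drug, phase or subgroup is named, so the sentence covers both arms.

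On duration, the abstract (Methods) says: "Standard treatment for 7 days followed up for 30 days at the same time". Section 2.5 gives no course length but does give the follow-up: "all patients will be followed up for 30 d by telephone or outpatient clinic". Section 2.7 lists the assessment times ("Data will be collected before treatment, 72 hours after treatment, and at the end of treatment according to evaluation criteria") and then adds: "After 30 days of treatment, outpatient or telephone follow-up will be conducted for each patient".

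**The concern.** Once daily and once a week cannot both be followed by the same patient on the same drug. The two statements stand in one section, and neither is qualified.

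Frequency and number of infusions are part of the definition of the intervention. In this trial they define both arms: furosemide is common to the two groups, and Shenfu is the added component whose effect is to be estimated. If the planned schedule is not fixed, three things follow:

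- Whoever writes the infusion order has to choose between two sentences of the protocol, and the article gives no rule for the choice.
- There is no planned number of infusions against which adherence or a deviation could be judged.
- A reader of the eventual result cannot tell from the protocol which regimen was meant to be tested.

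The section 2.7 wording is a smaller matter. Taken literally, its phrase about 30 days describes the length of treatment, which would disagree with the abstract.

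**Working it through.** The plan states no planned number of infusions, so there is no figure to reproduce. The check is a count under each stated frequency.

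**Inputs**

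- Frequency A: 1 infusion per day, from the drug orders in section 2.5.
- Frequency B: 1 infusion per 7 days, from the later sentence in section 2.5.
- Course length L = 7 days, from the abstract. This is the only duration in the article that is given plainly as treatment and is not contradicted by another description of the same period.

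**Count on the 7-day course**

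- Daily: 7 days × 1 per day = 7 infusions.
- Weekly: 7 days × 1 per 7 days = 1 infusion.
- Ratio: 7 / 1 = 7.

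If the amount per infusion is the same under both readings, the ratio of planned cumulative exposure is also 7. It applies to Shenfu in the observation group and to furosemide in both groups.

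**Do the 30 days describe treatment or follow-up?**

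| Place | How the 30 days are described |
|---|---|
| Abstract, Methods | follow-up, alongside 7 days of treatment |
| Section 2.5 | follow-up, by telephone or outpatient clinic |
| Section 2.7 | literally a period of treatment, in a sentence whose subject is outpatient or telephone follow-up |

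Two of the three places call the 30 days follow-up. The third is itself about follow-up, and it comes after a sentence that already lists an assessment when treatment ends. The likely meaning of section 2.7 is therefore 30 days of follow-up, loosely worded. It needs correcting so that it cannot be read as course length, but it is not good evidence for a 30-day course.

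**The case against.** The strongest reply is that the weekly sentence is a slip. The abstract gives a course of 7 days, so the sentence may have been meant to say that infusions continue for one week. The frequency is daily at every drug order, and the weekly sentence stands alone. This is plausible. The article does not confirm it, however, and a regimen that has to be inferred by guessing at a slip is not fixed. The objection makes the correction easy; it does not make it unnecessary.

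A second reply is that section 2.5 plans a dedicated drug manager and detailed recording of all interventions for the analysis. This stands in part. Exposure actually given should be recoverable, and nothing shows that patients within an arm would in fact be treated differently. It would go too far to say that adverse reactions could not be related to exposure. The weekly sentence also applies to everyone, so it creates no difference in furosemide schedule between the arms. But a record of what was given does not say what was planned.

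A third reply is that a journal article condenses the full protocol. That would excuse leaving the course length out of section 2.5, since the abstract states it. It does not excuse two incompatible frequencies, because nothing has been left out there.

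Some stronger readings are tempting but not supported:

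- **A 30-day course with 1 to 30 infusions across readings.** A reader might take this from section 2.7. It depends on reading 30 days as treatment, against the abstract and section 2.5.
- **A difference of at least sevenfold.** This fails even if a 30-day course is allowed. Weekly doses on days 1, 8, 15, 22 and 29 make 5 infusions, and 30 / 5 = 6. Counting only complete weeks gives 30 / 4 = 7.5. Daily dosing for 7 days against weekly dosing for 30 days gives only 7 / 5 = 1.4 to 7 / 4 = 1.75. Sevenfold is exact for the 7-day course and is not a lower bound over all readings.
- **A shift in what the 72-hour assessment measures.** A reader might argue that it falls mid-course under daily dosing but after the only infusion under weekly dosing. That assumes the 72 hours run from the first infusion, which section 2.7 does not say.

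**Conclusion.** The point holds for infusion frequency: section 2.5 is wrong as written. It prescribes daily infusions in every drug order and weekly infusions for all patients, and no other text resolves the conflict. On the abstract's 7-day course the planned number of infusions is 7 or 1, a sevenfold difference in planned cumulative exposure to Shenfu in the observation group and to furosemide in both groups.

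The size rests on two assumptions: that the course is 7 days, as the abstract states, and that the amount per infusion is the same under either frequency. The contradiction itself rests on neither.

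The 30-day phrase in section 2.7 is a secondary wording fault, probably meaning follow-up. The documents do not establish a second course length, and they do not show that patients would in practice receive different schedules. Because the conflict concerns what both arms receive, it must be settled before anyone is treated.

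**What to change.** Before the first patient, the sponsor should reconcile the abstract, section 2.5 and section 2.7 so that the following are stated consistently:

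- one infusion frequency for each study drug;
- one course length in days;
- the resulting planned number of infusions per patient.

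The section 2.7 phrase about 30 days should be reworded to agree with the reconciled course and follow-up periods, so that it cannot be taken for a different course length. The infusion order sheet should carry the same schedule.

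Which of the two frequencies is intended is for the sponsor to state; no view on that is taken here. Section 2.5 already plans to record all interventions, so no new data item is needed.

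The cost is a wording correction in three places and a matching order sheet, with no extra patients, visits or procedures.

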### Evaluation criteria and efficacy judgment

2.6

1.Main outcome measures: ① total effective rate of cardiac function improvement (refer to the guiding principles of clinical research of new drugs in traditional Chinese medicine^[11]^), Excellent: heart failure was essentially ameliorated or the NYHA classification increased by at least 2 levels; Valid: NYHA classification increased by 1 level; Invalid: NYHA classification remained the same before and after the treatment. Worsened: NYHA classification decreased by at least.2.Secondary outcome measures: left ventricular ejection fraction (LVEF), N-terminal pro-brain natriuretic peptide (NT-pro BNP), tumor necrosis factor-*α* (TNF-*α*), Interleukin-6(IL-6), and 6-minute walk test.3.Adverse reactions, including abnormal liver and kidney function and any discomfort during treatment (such as dizziness, nausea, etc.).

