### Patients

2.3

Inclusion criteria: ① meet the diagnostic criteria of coronary heart disease, the patients had occlusive myocardial infarction, and the stenosis rate of the main branch of the coronary artery (at least one branch) is more than 50%;) ② meet the diagnostic criteria for chronic heart failure.^[2]^ Doppler echocardiography indicated that the left ventricular ejection fraction was less than 50%;^[10]^③ The age was 40 to 79 years; ④ New York Heart Association (NYHA) grade III–IV; ⑤ No myocardial infarction and angina pectoris occurred in the past month.

Exclusion criteria: ① Patients with heart failure induced by other diseases such as congenital heart disease; ② Complicated with other serious diseases such as malignant tumor; ③ Other heart diseases such as severe arrhythmia; ④ Complicated with serious mental illness; ⑤ Patients with drug allergy or contraindications in this study; ⑥ Unable to understand the study protocol or unwilling to participate in the study after explanation.

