### Statistical analysis

2.8

Data will be analyzed according to the full analysis set principle. Fisher exact test and the Mann–Whitney U test will be performed for comparison of both groups, for categorical variables and continuous variables, respectively. When *P* < .05, the difference will be statistically significant.

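### The primary outcome is worded with the NYHA direction reversed, so patients entering at class III–IV who improve are not coded as successes by the NYHA criteria, and III to IV is

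*Protocol article*

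**What the plan says.** Protocol article, section 2.6 (Evaluation criteria and efficacy judgment), lists one main outcome, the "total effective rate of cardiac function improvement". It refers to external guiding principles for clinical research of new traditional Chinese medicines and then sets out four grades. The two favourable ones, *Excellent* and *Valid*, are defined one after the other: "heart failure was essentially ameliorated or the NYHA classification increased by at least 2 levels; Valid: NYHA classification increased by 1 level". Patients whose class does not change are graded *Invalid*. The last grade covers a fall in class: "Worsened: NYHA classification decreased by at least". There the sentence ends, in the text as shown, without a number of levels.

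Section 2.3 (Patients) limits entry to "New York Heart Association (NYHA) grade III–IV".

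No other section reverses the NYHA scale, says that a rise means an improvement, or states which grades are added to give the total effective rate.

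**The concern.** NYHA class is a severity scale: I is least limited and IV most severe. A rule that rewards a rise in class and penalises a fall therefore points the wrong way. The entry criterion makes the conflict plain, because patients start in the two highest classes and have almost no room to rise.

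This is the operative definition of the only main outcome, and section 2.7 has assistants collect the data against these criteria. If they apply the text as written, patients who benefit can be recorded as worsened and patients who deteriorate as responders. If they quietly turn the rule round, the endpoint that is analysed is not the one that was published. Either way, a reader of the results cannot tell from the protocol how the primary outcome was coded.

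**Working it through.** The plan gives no figure to reproduce here, because the question is how a classification rule behaves. The check lists every possible transition and grades it twice.

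**Inputs**
- Baseline classes: III and IV (section 2.3).
- Grades: as in section 2.6.
- Scale: four classes, IV the most severe. The article does not spell this out, so it is an assumption, though the standard one.
- Threshold for *Worsened*: missing in the text as shown, and taken as 1 level at first.

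**Rule.** Let d = class after treatment minus class before.
- As written: d ≥ 2 *Excellent*; d = 1 *Valid*; d = 0 *Invalid*; d ≤ −1 *Worsened*.
- Direction reversed: the same cut-offs applied to −d.

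| Before → after | d | What happened | As written | Direction reversed |
|---|---|---|---|---|
| III → I | −2 | improved | Worsened | Excellent |
| III → II | −1 | improved | Worsened | Valid |
| III → III | 0 | unchanged | Invalid | Invalid |
| III → IV | +1 | deteriorated | Valid | Worsened |
| IV → I | −3 | improved | Worsened | Excellent |
| IV → II | −2 | improved | Worsened | Excellent |
| IV → III | −1 | improved | Worsened | Valid |
| IV → IV | 0 | unchanged | Invalid | Invalid |

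**Results**
1. The largest possible rise is IV − III = 1 level from class III and IV − IV = 0 from class IV. A rise of 2 is out of reach for every eligible patient. This needs only that IV is the highest number, whichever end is severe.
2. The only transition graded *Valid* is III → IV, the one possible deterioration.
3. All 5 improving transitions are graded *Worsened*. With the deterioration, 5 + 1 = 6 of the 6 transitions that involve a change are misgraded. Only *no change* is graded the same way in both columns.
4. With the direction reversed, all four grades can be reached from the eligible classes.

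**Missing number of levels.** If the number for *Worsened* were 2, III → I, IV → I and IV → II would be *Worsened*, and III → II and IV → III would have no grade. Whatever the number, no improving transition becomes a success through NYHA class.

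**Amelioration route.** The first half of *Excellent* is joined to the NYHA criterion by an *or* and carries no class threshold. A patient who moves from IV to II and is judged essentially ameliorated is *Excellent* by that route and *Worsened* by NYHA class.

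**Hypothetical size.** Suppose 70% of patients improve by at least one class, 25% are unchanged and 5% deteriorate. These figures come from no document. Let f be the share of improvers judged essentially ameliorated and counted as *Excellent*, and assume that only improvers can be so judged. Reading the total effective rate as *Excellent* + *Valid*:
- Intended rate = 70%.
- Literal rate = 5% + f × 70%, that is 5% at f = 0 and 5% + 70% = 75% at f = 1.

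The literal rate thus depends almost wholly on a judgement that the article does not define.

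**The case against.** The strongest reply is that the intended direction is clear from section 2.6 itself. The outcome is named as an improvement, the rises carry the favourable labels, the two-level rise stands beside essential amelioration of heart failure, and the fall is labelled as worsening. A rise of two levels from class III or IV is so plainly impossible that an assessor would hardly apply it literally. This looks like a translation slip for improved and worsened. The cited guiding principles, which are not available here, may state the direction correctly.

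Most of that stands, and it limits the consequence. A reader might infer that the trial will count deterioration as success and reach a primary conclusion with the wrong sign. The article does not support that as a certainty. It would require assessors to code III to IV as a response under an outcome called improvement, and the amelioration route, which is not reversed, can still count improved patients as successes. A reader might also infer that patients who die drop out of the rate because no grade names death. The article does not say so. Section 2.8 refers only to the full analysis set, and the handling of deaths may sit in an analysis plan that is not shown.

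What the reply does not remove is that the operative text contradicts itself, that no other section corrects it, and that a reference to outside criteria does not settle which of the two applies.

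**Conclusion.** The point holds as an error in the stated definition of the primary outcome. Read literally for a class III–IV population, the NYHA part of *Excellent* is unattainable, *Valid* can be reached only by deteriorating, and none of the 5 improving transitions is a success through NYHA class. All 5 are *Worsened* if the missing threshold is one level. The grades are also not mutually exclusive, because the amelioration route has no threshold.

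The practical consequence is a risk of miscoding, or of an analysed endpoint that differs from the published one. A wrong-sign result is possible but not established.

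The conclusion rests on the standard orientation of the NYHA scale. The list of transitions needs no assumed response rates; the 5% to 75% range in the illustration does, and it is hypothetical. That the total effective rate is *Excellent* plus *Valid* is the natural reading of the labels, but the article does not state it. The definition should be corrected before any outcome is coded.

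**What to change.** Reword the main-outcome paragraph in section 2.6:

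- State that improvement means a numerically lower NYHA class after treatment than before, and worsening a numerically higher one.
- *Excellent*: lower by 2 or more classes. *Valid*: lower by 1. *Invalid*: unchanged. *Worsened*: higher by 1 or more. One level is the workable threshold for *Worsened*, because III to IV is the only deterioration open to these patients and a threshold of two would leave the grade empty.
- State that the total effective rate is *Excellent* + *Valid*.
- Define essential amelioration in line with the cited guiding principles, so that each patient falls into exactly one grade.

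The cost is one paragraph of wording and a matching instruction to the assistants who collect the outcome. No extra data or patients are needed.

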### Data collection and management

2.7

Data will be collected before treatment, 72 hours after treatment, and at the end of treatment according to evaluation criteria. After 30 days of treatment, outpatient or telephone follow-up will be conducted for each patient. Detailed follow-up information can not be collected to record the reasons for loss of follow-up information. All data will be collected by one or two assistants. Personal information about potential and registered participants will be collected, shared, and kept in a separate storeroom to protect confidentiality before, during, and after the trial. Access to the database will be limited to the researchers of this research group.

### Statistical analysis

2.8

Data will be analyzed according to the full analysis set principle. Fisher exact test and the Mann–Whitney U test will be performed for comparison of both groups, for categorical variables and continuous variables, respectively. When *P* < .05, the difference will be statistically significant.

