### Sample size calculation

2.4

This study is a pilot clinical trial. The calculation of the sample size will be based on a drop-out rate of 20% in the clinical study, and 0.025% of the sample size will be taken as 90%, which is calculated to include 110 patients. The patient will randomly select any number from 001 to 110 from the sealed envelope and is assigned to the observation group (odd) and the control group (even) according to the parity of the number.

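### Continuous secondary outcomes are compared by a Mann–Whitney test with no baseline covariate, although a pre-treatment value is planned for each: a valid test, but less precise than a baseline-adjusted analysis

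*Protocol article*

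**What the plan says.** Section 2.8 (Statistical analysis) names one between-group method for each type of variable: "Fisher exact test and the Mann–Whitney U test will be performed for comparison of both groups, for categorical variables and continuous variables, respectively". It mentions no covariate or model, and it does not say which quantity enters the test (end value, change from baseline, or the 72-hour value). The threshold is given as "When *P* < .05, the difference will be statistically significant", without stating one- or two-sided.

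Section 2.6 lists the outcomes to which this applies. The list opens with "Secondary outcome measures: left ventricular ejection fraction (LVEF), N-terminal pro-brain natriuretic peptide (NT-pro BNP" and continues with TNF-α, IL-6 and the 6-minute walk test. All five are continuous as measured.

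A baseline value is planned for them. Section 2.7: "Data will be collected before treatment, 72 hours after treatment, and at the end of treatment according to evaluation criteria". Section 2.5: "The health status of each patient will be evaluated before and after treatment, including efficacy and safety indicators".

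**The concern.** The trial will hold a pre-treatment value of each continuous outcome, and the treatment period is only 7 days. If a patient's starting value predicts the end value, part of the spread in end values is known before treatment begins. A two-sample rank test on end values leaves that spread in the comparison. A test on changes subtracts the whole baseline, which over-corrects unless the correlation is perfect.

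Two things are at stake: power on the laboratory, imaging and walking measures, and the reading of any single result when the arms happen to differ at baseline. Section 2.4 allocates by the parity of a drawn number and describes no stratification, so such differences are left to chance.

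**Working it through.** **Inputs from the document.** The total is 110 patients, allocated 1:1 (abstract, section 2.4). The calculation is "based on a drop-out rate of 20% in the clinical study". The threshold is 0.05 (section 2.8).

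**Inputs assumed.** The document gives none of these: true effect 0.5 SD; two-sided test; correlation ρ between baseline and end value of 0.3, 0.5, 0.7 or 0.8; normally distributed values with equal variance at both times.

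**The plan's own figure.** Only the dropout step can be checked: 88 / (1 − 0.20) = 110, so 88 patients, or 44 per arm, remain. The 110 itself cannot be derived. No effect size is stated, and the wording on error rates ("0.025% of the sample size will be taken as 90"%) cannot be read as it stands. The point does not depend on how 110 was reached.

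**Variance of the treatment comparison, relative to end values.**
- End value: 1
- Change from baseline: 2(1 − ρ)
- ANCOVA: 1 − ρ²

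| ρ | Change | ANCOVA | ANCOVA ÷ change |
|---|---|---|---|
| 0.3 | 1.40 | 0.91 | 0.65 |
| 0.5 | 1.00 | 0.75 | 0.75 |
| 0.7 | 0.60 | 0.51 | 0.85 |
| 0.8 | 0.40 | 0.36 | 0.90 |

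ANCOVA has the smallest variance in every row. Change scores do worse than end values below ρ = 0.5.

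**Power by formula.** Power ≈ Φ(0.5 / √(v × 2/44) − 1.96), where v is the relative variance. For a Mann–Whitney test v is multiplied by π/3 = 1.047.
- Mann–Whitney, end values: 0.5 / √(1.047 × 0.04545) = 2.29, giving Φ(0.33) = 63%.
- ANCOVA, ρ = 0.7: 0.5 / √(0.51 × 0.04545) = 3.28, giving Φ(1.32) = 91%.

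**Power by simulation** (4,000 trials per setting, 44 per arm; within about 3 points of the formula).

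| ρ | Mann–Whitney, end values | Mann–Whitney, changes | ANCOVA | Rank ANCOVA |
|---|---|---|---|---|
| 0.3 | 61% | 47% | 67% | 64% |
| 0.5 | 62% | 61% | 76% | 73% |
| 0.7 | 63% | 84% | 90% | 87% |
| 0.8 | 63% | 94% | 97% | 95% |

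**Type I error.** With no effect, and averaged over randomisations, all four methods reject in about 5% of trials (4.2% to 5.3% in the simulations).

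**Chance imbalance.** The standard error of a baseline difference is √(2/44) = 0.213 SD. A difference above 0.3 SD in either direction has probability 2[1 − Φ(0.3/0.213)] = 16%; above 0.2 SD, 35%. A baseline difference δ shifts the end-value comparison by ρδ and the change comparison by (ρ − 1)δ, and leaves ANCOVA unshifted. At δ = 0.3 and ρ = 0.7 the shifts are 0.21 SD and −0.09 SD. Given a 0.3 SD imbalance and no effect (2,000 trials per ρ), Mann–Whitney rejects in 6–9% of trials on end values and 5–7% on changes, against 4.5–6% for ANCOVA.

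**The case against.** The strongest objection is that nothing here is an error. A reader might infer that the planned test is biased or inflates false positives. It does not: under randomisation it holds its level, and even given a 0.3 SD imbalance the excess is a few percentage points. That stands, so the point concerns precision and the reading of one realised result.

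A reader might also infer that the plan ignores baseline altogether. The document does not support that. It leaves open whether changes are tested, and if they are, baseline is partly used. At ρ = 0.8 the gap to ANCOVA is then only 94% against 97%. But adjustment is the more precise choice on both readings at every correlation examined.

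The magnitude is assumed. Nothing in the document shows that these outcomes correlate strongly over 7 days, and restricting entry to LVEF below 50% and NYHA III–IV could weaken some correlations. At ρ = 0.3 ANCOVA gains only about 6 points over end values. The 44 per arm is also inferred from the dropout allowance, whereas section 2.8 specifies a full analysis set. With 55 per arm the same formula gives about 73% for Mann–Whitney on end values and 79/86/96/99% for ANCOVA. The levels rise but the ordering is unchanged.

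Covariate lists, transformations and interval estimates are commonly left to an analysis plan, so their absence from the article is not counted here. What is counted is the method that section 2.8 does name. Finally, only secondary outcomes of a self-described pilot are affected. The main outcome is a change in NYHA class from the patient's own starting class, so it already uses baseline.

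**Conclusion.** The point holds as one of efficiency. Section 2.8 fixes a test without a covariate for five outcomes that each have a planned baseline. Whether end values or changes are tested, a baseline-adjusted analysis is more precise for correlations from 0.3 to 0.8 and deals better with chance imbalance.

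Under the assumptions above, the power gain of ANCOVA over Mann–Whitney on end values is about 6 points at ρ = 0.3, 13 to 14 at 0.5, 28 at 0.7 and 34 at 0.8. Over Mann–Whitney on changes it is about 19, 14, 7 and 2 points (differences of the unrounded simulated powers). These figures show how the gain depends on an unknown correlation; they do not forecast it for this trial. The planned test remains valid, and the main outcome is untouched.

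**What to change.** In section 2.8, prespecify for each continuous secondary outcome an ANCOVA of the end-of-treatment value on arm and that outcome's own baseline value. Fix in advance that NT-proBNP, TNF-α and IL-6 are analysed on the log scale. Report the adjusted difference, or the adjusted ratio for the logged outcomes, with a 95% confidence interval.

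Keep the Mann–Whitney test, or rank ANCOVA, as a sensitivity analysis named beforehand, and say which quantity it is applied to. It should not be brought in after looking at residuals, since that makes the choice of method depend on the data. NYHA class as a further covariate is optional.

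The cost is a change of wording, slightly more analysis work and a modelling assumption, for secondary outcomes only. It needs no new data or visits, and SPSS 25.0, named in the abstract, can fit the model.

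### The unadjusted Fisher test on the total effective rate is valid but conservative (true size about 3% at most) and ignores baseline NYHA class; an adjusted test or Boschloo's test would use the same data better

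*Protocol article*

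**What the plan says.** Section 2.6 names the main outcome as the "total effective rate of cardiac function improvement". It is built from four grades of change in NYHA class (Excellent, Valid, Invalid, Worsened), each relative to the patient's own starting class; for example, "Invalid: NYHA classification remained the same before and after the treatment". The article does not say which grades count as effective. Excellent plus Valid is the natural reading and is assumed here.

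Section 2.3 admits patients in "New York Heart Association (NYHA) grade III–IV", so baseline class has two levels.

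Section 2.8 states that "Fisher exact test and the Mann–Whitney U test will be performed for comparison of both groups", "for categorical variables and continuous variables, respectively", and that "When *P* < .05, the difference will be statistically significant". It names no stratification factor or covariate and does not mention ordered categories. Section 2.4 plans 110 patients with a "drop-out rate of 20% in the clinical study"; allocation is by odd or even envelope number and is not stratified by NYHA class.

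**The concern.** Fisher's test conditions on both margins of the 2x2 table. With groups of this size few P values are attainable, so the chance of a false positive falls well below the nominal 5%. That unused error rate is lost power, and other tests can recover part of it from the same data.

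The named test also makes no use of baseline NYHA class. Class is known for every patient, and the outcome is defined as change from it. If the chance of improving differs between class III and class IV, an unadjusted comparison leaves that variation in the error. At stake is the power of the main comparison in a small trial. The validity of its P value is not in question.

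**Working it through.** **The plan's own figure.** With 20% dropout, 110 × (1 − 0.20) = 88, or 44 per arm; conversely 88 / 0.80 = 110. The 88 cannot be derived, because section 2.4 gives no response rates or effect size and its statement of error and power is unclear ("0.025% of the sample size will be taken as 90" per cent). All response rates below are therefore assumptions. Results are shown at 44 per arm (dropouts lost) and 55 per arm (everyone analysed), at two-sided 0.05; the article does not state sidedness.

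**Step 1: true size of Fisher on the 2x2 table.** With n per arm and common rate p, size = Σ Bin(x; n, p) · Bin(y; n, p) over all pairs (x, y) with Fisher P ≤ 0.05, by exact enumeration.

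| Common rate | 44 per arm | 55 per arm |
|---|---|---|
| 50% | 2.6% | 2.8% |
| 60% | 2.9% | 3.0% |
| 70% | 2.9% | 3.1% |
| 80% | 2.5% | 2.7% |
| 90% | 1.9% | 2.0% |
| 95% | 0.5% | 0.9% |

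Over all common rates the maximum is 3.06% at 44 per arm and 3.19% at 55.

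**Step 2: Boschloo's test.** It uses Fisher's P value as its statistic but sets the cut-off so that the maximum size over all common rates stays at or below 5%. The cut-off becomes 0.0734 at 44 per arm and 0.0732 at 55, with maximum sizes of 4.78% and 4.73%. Exact power:

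| Control vs SFI rate | 44: Fisher → Boschloo | 55: Fisher → Boschloo |
|---|---|---|
| 50% vs 80% | 80.2 → 84.9 | 89.1 → 91.8 |
| 60% vs 80% | 44.8 → 53.3 | 56.0 → 62.6 |
| 60% vs 85% | 68.0 → 75.5 | 79.8 → 84.1 |
| 60% vs 90% | 87.9 → 92.0 | 94.8 → 96.4 |
| 70% vs 90% | 56.1 → 64.9 | 68.2 → 75.1 |
| 70% vs 95% | 85.4 → 89.5 | 92.9 → 95.5 |
| 75% vs 90% | 35.2 → 43.5 | 44.7 → 53.4 |

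The gain is about 4 to 9 points at 44 per arm and 2 to 9 at 55. It is smallest where power is already high.

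**Step 3: adjusting for baseline NYHA class.** Simulation of 6,000 trials per row, with half the patients in each class and an odds ratio of 3.5 within class (all assumed). Entries are power in %, as Fisher / unadjusted chi-square / Cochran–Mantel–Haenszel (CMH).

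| Control rate in the two classes | 44 per arm | 55 per arm |
|---|---|---|
| 60%, 60% | 62.5 / 72.2 / 70.9 | 75.8 / 81.6 / 81.1 |
| 50%, 75% | 56.7 / 67.9 / 68.8 | 69.4 / 76.2 / 78.4 |
| 40%, 85% | 45.2 / 56.6 / 62.8 | 57.8 / 66.2 / 73.3 |

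Stratification itself (CMH minus chi-square) contributes from −1.3 points when class is not prognostic (70.9 − 72.2) to +7.1 when it strongly is (73.3 − 66.2). CMH exceeds Fisher by more, but the rest of that gap comes from running near 5% instead of 3%. With no treatment effect, CMH rejected in 4.6% to 5.2% of simulated trials.

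**Step 4: using the order of the grades.** Simulated power at 44 per arm, with a common odds ratio of 3 and three assumed control distributions: ordinal rank test 64–79%, Fisher on the 2x4 table 50–65%, Fisher on the collapsed 2x2 table 35–54%. At 55 per arm: 74–87%, 59–74% and 46–66%. The 2x4 Fisher test has simulated size 4.5–5.4%, so the 3% figure belongs to the 2x2 table only.

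**The case against.** Fisher's test is a legitimate choice. It guarantees size at or below 5%, which the unadjusted chi-square test does not: at 44 per arm that test reaches 5.2% to 5.9% for several common rates. Allocation is not stratified by NYHA class, so an unadjusted test matches the design. Covariate adjustment is often left to an analysis plan that is not shown here. The trial calls itself a pilot and states no effect size, so no target power can be shown to be missed. All of this stands, and it limits the point to efficiency.

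A reader might infer three stronger things that the article does not support:

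- **That a four-level ordinal primary outcome is being given the wrong test.** The named outcome is a rate. Order is lost when the grades are collapsed into that rate, which is a choice of endpoint and not a fault of Fisher's test. No single reading combines a four-level outcome with a 3% size.
- **That baseline class caps the improvement a patient can show.** It does not under these grades. III to I and IV to II are both two classes, so patients in either class can reach Excellent. The reason to adjust is that class may be prognostic, and the article gives no data on that.
- **That Fisher brings no benefit.** Its guaranteed size is one.

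The ordinal figures also assume proportional odds, which favours the rank test.

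**Conclusion.** The point holds as an improvement in efficiency; section 2.8 contains no statistical error here. A named, unadjusted Fisher test on the total effective rate spends at most about 3% of the 5% allowed. Boschloo's test keeps the exact guarantee and is more powerful in every case examined. The benefit of adjusting for NYHA class is less certain: it may be nil, it could be about 7 points, and in the cases examined the loss is about 1 point.

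These sizes rest on a two-sided 0.05 level, on Excellent plus Valid counting as effective, on 44 to 55 analysed patients per arm, and on assumed response rates. The ordinal comparison could have clearly more power than either form of Fisher's test, but making it primary would change what the trial estimates. That is a trade-off for the sponsor.

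**What to change.** In section 2.6, state that the total effective rate is the proportion graded Excellent or Valid, and keep it as primary. In section 2.8, replace Fisher for this outcome with one prespecified analysis:

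- a Cochran–Mantel–Haenszel test stratified by baseline NYHA class (III, IV), or logistic regression with baseline NYHA class as covariate; or
- Boschloo's test, if an unadjusted exact test is preferred.

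Report the effective rate in each arm and the rate difference with a 95% CI. Add an ordinal comparison of the four grades as a supportive analysis: Mann–Whitney, van Elteren stratified by NYHA class, or a proportional-odds model. This needs the definition of Worsened completed, because as printed it gives no number of classes.

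The cost is a change of wording and slightly more analysis work, with no extra patients, visits or data. The one real concession is that the adjusted tests are asymptotic and give up Fisher's exact guarantee on size; Boschloo's test does not.
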